### Economic evaluation

The economic evaluation will estimate the costs and cost-effectiveness of CAU + AOT compared with CAU alone over the 12-month follow-up. The primary economic evaluation will take a societal perspective including the use of all health and social care services, plus productivity losses (time off work due to illness) and criminal justice sector resources, known to be of particular importance in drug and alcohol populations. Whilst the NHS/personal social services perspective is generally preferred by National Institute for Health and Care Excellence (NICE), the inclusion of criminal justice sector resources is recognised by NICE as an appropriate extension for drug and alcohol treatment evaluations [34].

Resource use data is being measured using a version of the AD-SUS which was developed for addiction and alcohol use disorder populations in previous research [31]. The AD-SUS is completed in interview with participants at baseline (covering the previous 6 months) and at 6 and 12-month follow-up (covering the period since previous interview). Appropriate unit costs will be applied to all resource elements reported by participants to calculate the total cost per participant. The AOT intervention will be costed directly, taking a micro-costing approach and nationally applicable unit costs will be applied to all other health and social care services used (for example, NHS Trust reference costs and the Personal Social Services Research Unit Costs of Health and Social Care compendium [35]. Criminal activity will be costed using existing Home Office estimates [36], uprated as appropriate, unless newer estimates become available. Productivity losses will be valued using the human capital approach, which involves multiplying time off work due to illness by an appropriate wage rate [37].

Health utility is being measured with the EQ-5D-5 L (five dimensions, five levels) version of the EuroQol measure of health-related quality of life. The EQ-5D is a measure capable of generating quality adjusted life years (QALYs) for use in economic evaluations and will be used in the primary economic evaluation exploring cost-effectiveness in terms of cost per QALY. Responses will generate health states that utility weights can then be applied to and QALYs will be calculated using the total area under the curve approach. EQ-5D-5 L is a more sensitive version of the EQ-5D, measuring health-related quality of life and has been used extensively in previous alcohol studies in the UK (e.g. UKATT Research Team [33]).

Two economic evaluations will be carried out: a cost-utility analysis using quality adjusted life years calculated from the EQ-5D-5 L [38] using the area under the curve approach [39] (primary) and a cost-effectiveness analysis using the primary clinical measure of the RCT, percentage days abstinent in the past 90 days using the Time Line Follow Back interview (secondary). Cost-effectiveness will be assessed through the calculation of incremental cost-effectiveness ratios (ICER) – the additional costs of one intervention compared to another divided by the additional effects of one intervention compared to another [40]. Uncertainty will be represented by cost-effectiveness acceptability curves [41]. Analyses will use standard parametric tests with mean differences and 95% confidence intervals generated from bootstrap regressions (1000 replications) to account for non-normal distribution common to economic data [42, 43]. In line with the clinical analyses, all economic analyses will be conducted by intention to treat principles with stratification variables, SADQ and site as covariates and multiple imputation by chained equations to account for missing data. Sensitivity analysis will explore the impact of missing data using a complete case approach and the impact of perspective taking the narrower NHS/personal social services.

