### Baseline assessment

(i)Socio-demographic information: age, sex, ethnicity, marital status, living arrangement, children, living arrangements of children, education.(ii)Drinking in the previous 90 days – TLFB 90I [23]. The TLFB is a validated interview method to measure alcohol consumption in the previous 90 days and is the gold standard outcome measure in alcohol treatment research. Percentage days abstinent, units of alcohol per drinking day (1 UK unit = 8 g alcohol), time to first alcoholic drink, relapse to any drinking and relapse to heavy drinking (8+/6+ units for males/females on a single occasion) will be computed.(iii)History of drug use – TLFB.(iv)Alcohol related problems - Alcohol Problems Questionnaire (APQ) [24]. The APQ is a validated 46-item questionnaire assessing potential problems with psychological, physical, social, legal, employment, relationships and parenting that may be experienced due to alcohol.(v)Severity of alcohol dependence - Severity of Alcohol Dependence Questionnaire (SADQ) [25]. The SADQ is a validated 20-item self-complete questionnaire containing items representing five domains of the alcohol dependence syndrome: (i) physical withdrawal signs (ii) psychological withdrawal signs (iii) withdrawal relief drinking (iv) tolerance (v) reinstatement following a period of abstinence.(vi)Health related quality of life – EuroQol 5 dimensions 5 levels (EQ-5D-5 L) [26]. The EQ-5D-5 L consists of five dimensions (mobility, self-care, usual activities, pain/discomfort and anxiety/depression) scored on five levels (no problems, slight problems, moderate problems, severe problems and extreme problems). The EQ-5D-5 L is an extension of the original 3-level EQ-5D and has been shown to be valid [27].

This version of EuroQol measure of health-related quality of life capable of generating quality adjusted life years (QALYs) for use in economic evaluations.

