### Follow up assessments

Six and twelve months after randomisation, all participants will be followed up (see Fig. 1). A research worker, blind to treatment allocation, will arrange a convenient time to meet with the participant. Baseline measures (items i-x above) will be repeated in addition to:
(xi)Therapeutic relationship – Scale to assess therapeutic relationship (STAR) [32] completed at 12 months follow-up. Therapeutic relationship (or alliance) has been found to predict clinical outcome across a range of mental disorders including alcohol dependence. This will be used as an additional process measure to assess the impact of therapeutic relationship on medication adherence and clinical outcome.

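### The named economic covariates leave out baseline EQ-5D-5L utility, which carries a quarter of the weight in the QALY; adding it costs nothing and gains precision and conditional balance

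*Protocol article*

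**What the plan says.** All references are to the protocol article.

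- **Covariates.** Economic evaluation states one list for every economic analysis: "all economic analyses will be conducted by intention to treat principles with stratification variables, SADQ and site as covariates". Neither baseline utility nor baseline cost is named there or elsewhere as a covariate.
- **Outcome.** The primary economic evaluation is "a cost-utility analysis using quality adjusted life years calculated from the EQ-5D-5 L", and "QALYs will be calculated using the total area under the curve approach".
- **Timing of utility.** Baseline assessment lists "Health related quality of life – EuroQol 5 dimensions 5 levels" as item vi. Follow up assessments, at 6 and 12 months, says "Baseline measures (items i-x above) will be repeated in addition to" the therapeutic relationship scale. Utility is therefore available at 0, 6 and 12 months.
- **Baseline cost.** AD-SUS is also taken at baseline and looks back over six months, so a pre-randomisation cost can be calculated for each participant.
- **Balance by design.** Randomisation and blinding stratifies by site and by SADQ (up to 30, above 30). Utility and cost are not stratification factors.
- **Sensitivity analyses.** The economic ones cover complete cases and the narrower NHS/personal social services perspective. Neither addresses baseline imbalance.

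**The concern.** An area-under-the-curve QALY contains the baseline utility as one of its terms. Treatment cannot change that term, but it differs between arms by chance. Without baseline utility in the regression, the chance difference enters the incremental QALY twice: arithmetically, through its own weight, and again because people with higher utility at baseline tend to have higher utility later.

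The incremental QALY feeds the primary economic result, the ICER and the acceptability curves. At stake are how precise that result is and how far it depends on an imbalance that is visible at baseline and could be adjusted for with data already collected.

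Baseline cost is a lesser matter. It is not a component of the 12-month cost and acts only through its correlation with later cost.

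**Working it through.** **Inputs from the protocol article.** Assessments at 0, 6 and 12 months; 80 randomised per arm (64 / 0.8 = 80, Sample size and power). The article gives no utility SD, no between-visit correlation and no expected QALY effect, so there is no figure of the plan's own to reproduce here.

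**Assumptions.** Utility SD 0.3 (range 0.20 to 0.35), equal at each visit; a common between-visit correlation r of 0.5 (0.4 to 0.6 for the precision figures). SADQ and site are left out of the calculation.

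**1. Weights.** The trapezoid rule over two half-year intervals gives

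QALY = 0.5 × (u0 + u6)/2 + 0.5 × (u6 + u12)/2 = 0.25 u0 + 0.50 u6 + 0.25 u12.

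**2. Size of a chance imbalance.** SE of the baseline difference = SD × sqrt(2/80).

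- SD 0.30: 0.30 × 0.158 = 0.047
- SD 0.20: 0.032
- SD 0.35: 0.055

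**3. Shift in the QALY difference for a one-SE imbalance.**

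- Direct: 0.25 × 0.047 = 0.012.
- Total, per unit of imbalance: 0.25 + 0.75r = 0.625 at r = 0.5. Then 0.625 × 0.047 = 0.030 (0.020 at SD 0.20, 0.035 at SD 0.35).

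**4. Precision.** In units of the squared SD, Var(QALY) = 0.375 + 0.625r. The share explained by u0 is R² = (0.25 + 0.75r)² / (0.375 + 0.625r), and the interval shrinks by the factor sqrt(1 − R²).

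| r | R² | Interval factor | Narrowing |
|---|---|---|---|
| 0.4 | 0.3025 / 0.625 = 0.484 | 0.718 | 28% |
| 0.5 | 0.3906 / 0.6875 = 0.568 | 0.657 | 34% |
| 0.6 | 0.49 / 0.75 = 0.653 | 0.589 | 41% |

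At SD 0.3, r = 0.5 and 80 per arm, the SE of the incremental QALY is 0.039 unadjusted and 0.026 adjusted.

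**5. Simulation check.** 20,000 trials with no treatment effect, 64 per arm, SD 0.3 and r = 0.5:

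- The mean unadjusted QALY difference was about 0.
- The slope of the estimate on the baseline imbalance was 0.628 unadjusted and 0.003 with u0 in the model.
- The SE was 0.044 unadjusted and 0.029 adjusted.

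**6. Baseline cost.** If r is now the correlation between baseline and later cost, adjustment removes r² of the variance: 9%, 25% or 49% at assumed values of 0.3, 0.5 or 0.7.

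**The case against.** **The list may not be exhaustive.** The article names SADQ and site but does not say that nothing else will be used. Its abstract speaks of control for baseline measures without naming them, and Statistical analysis expects the plan to be refined and finalised later. A later plan could therefore add these covariates. Still, the list is explicit and covers all economic analyses, and the abstract's general wording does not add a variable to it. The point improves a stated model; it does not complain of missing detail.

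**Randomisation already protects the estimate.** A reader might infer that the planned incremental QALY is biased, or that the ICER and acceptability curve would be driven by chance. The documents do not support that. The unadjusted estimate is unbiased over repeated trials, and its bootstrap interval already includes this chance variation: the 0.030 shift is about three quarters of the unadjusted SE of 0.039. What stands is the conditional shift given the observed imbalance, and the lost precision.

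**The figures rest on outside assumptions.** This stands. SADQ, as covariate and stratification factor, also absorbs whatever part of baseline utility correlates with it, so the shifts and the narrowing are upper-end. With no expected QALY effect in the article, the shift cannot be compared with the effect sought.

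**Cost is not parallel to utility.** This stands too. A reader might expect baseline cost imbalance to carry over in the same way, but there is no arithmetic link. Nor do the documents show that prior cost strongly predicts later cost. Selecting people for heavy recent use could even weaken that correlation, through restricted range and regression to the mean.

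**Conclusion.** The point holds as a free improvement to the primary economic analysis, not as an error that invalidates it. Baseline utility has weight 0.25 in the QALY and is absent from the stated covariates, and no planned sensitivity analysis covers the gap.

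On the assumptions given, a one-SE chance imbalance moves the incremental QALY by 0.012 directly and about 0.03 in total (0.02 to 0.035 over the SD range, at correlation 0.5). Adjustment would narrow its interval by up to about 28% to 41%. The weight follows from the article alone. The sizes depend on the assumed SD, the correlations and the omission of SADQ.

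For cost, the case is one of precision only, with an unknown gain. The argument should not be extended to the secondary cost-effectiveness analysis: percent days abstinent before the 12-month visit contains no baseline term, so the arithmetic here does not apply to it.

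**What to change.** In Economic evaluation, or in the final analysis plan, state that the QALY regression adjusts for baseline EQ-5D-5L utility together with SADQ and site. Include baseline utility in the imputation model, refit the adjusted regression in each bootstrap replicate, and take the ICER and acceptability curves from the adjusted increments.

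Secondarily, add baseline six-month AD-SUS cost to the cost regression alongside SADQ and site, described as a gain in precision only, and include it in the imputation model.

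Trial status says that analysis is under way, so the change should be dated and documented before anyone sees economic results by arm. The cost is a few lines of wording and code; both baseline measures are already in the assessment schedule.

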### Protocol amendments

The inclusion criteria changed during recruitment to also include patients with alcohol related frequent emergency department attendances.

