### Participants

#### Inclusion criteria

i)Age 18 years or over.ii)Able to understand English sufficiently well to obtain informed consent and complete the assessment instruments.iii)has had two or more admissions in any of the participating NHS trusts for at least one wholly attributable alcohol diagnoses within a 1 year period, OR; has had at least ten presentations to an emergency department in any of the participating NHS trusts within a 1 year period, OR; has had at least four presentations to an emergency department in any of the participating NHS trusts within a month, OR; has been admitted at least once for a wholly attributable alcohol diagnosis and had at least four presentations to an emergency department in any of the participating NHS trusts within a 1 year period.iv)International Classification of Diseases version 10 (ICD-10) diagnosis of alcohol dependence.v)Willing to provide informed consent to participate in the trial.vi)A resident of Lambeth and Southwark and admitted to one of the five participating NHS Trusts.

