### Identification and recruitment of potential participants

The AOT clinical team will work with informatics teams in the five NHS trusts (King’s College Hospital (KCH)-, Guy’s and St Thomas’ (GST)-, South London and Maudsley (SLaM)- and St George’s Healthcare (STG)- NHS Foundation Trusts; and Lewisham and Greenwich (LGT) NHS Trust) to identify HNHC ARFA based on primary or secondary clinical diagnoses of alcohol related admissions and number of admissions or emergency department attendances in the previous 12 months. This will also include the use of the clinical research information system (CRIS) within SLaM. The clinical team will also have access to electronic clinical records and discuss potentially eligible patients with clinicians in inpatient units in the five trusts, and the Alcohol Care Teams at KCH, STG and GST, to identify additional patients who meet the study criteria but are not captured by diagnostic criteria in electronic records.

Once potentially eligible patients have been identified, they will be contacted by the AOT clinical team and assessed for eligibility and informed about the potential to participate in the trial. They will be given the Patient Information Sheet and the trial will be explained verbally. Patients will be encouraged to ask questions or consult carers, relatives or their GP. If willing to proceed, eligible patients will be introduced to a member of the research team who will again explain the trial, confirm the patient’s eligibility, and obtain informed consent. The minimum period of time between informing the patients of the trial and obtaining consent will be 24 h. Patients unwilling to take part will be offered the standard CAU, including referral to local specialist addiction services.

Patients who provide informed consent will undergo a baseline research assessment conducted by the research team and will be randomised using an electronic trial management tool. In order to maintain blinding of researchers, the treatment allocation will be provided only to the AOT clinical team who will then initiate AOT treatment or referral to specialist addictions services as appropriate.

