### Randomisation and blinding

Randomisation to one of the two treatment arms will take place after consent and baseline data have been collected, by a remote electronic allocation system. Once baseline data has been submitted on the electronic device by the researcher, the system will email the randomised allocation to a member of the clinical team. The researchers will be blind to the allocated intervention throughout the trial. The online system will be developed and maintained by Codeface Ltd. Randomisation will be stratified by site and severity of alcohol dependence (< = 30 and > 30), as measured by the Severity of Alcohol Dependence Questionnaire (SADQ).

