### Statistical analysis

Our analysis of the primary outcome measure involves a comparison of the effectiveness of AOT + CAU versus CAU alone. Analysis will be conducted by intention to treat principles and the primary outcome measure will be percent days abstinent in the 90 days prior to 12 months follow up. AOT + CAU will be compared to CAU using analysis of covariance including stratification variables; SADQ and site as covariates. Multiple imputation and sensitivity analysis will be employed to assess the impact of missing data. Results will be presented as mean differences with associated 95% confidence intervals. Secondary analysis will address drinking and other outcomes at 6 and 12 months using appropriate modelling approaches and these will be adjusted for covariates; SADQ, site, age and gender. We will explore the association between engagement in treatment (measured by cumulative number of days in AOT and specialist alcohol treatment), readiness to change, and therapeutic alliance, and drinking outcomes using a linear regression adjusted for known confounders. As with most trials the analysis plan will be refined throughout the course of the study and the final analysis plan prepared and agreed by the research team and Trial Steering Committee.

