## Discussion

AOT models piloted with alcohol dependent patients have demonstrated significant reductions in alcohol consumption and use of unplanned NHS care, with increased engagement with alcohol treatment services, compared with patients receiving CAU. While AOT interventions are more costly per case than current standard care in the UK, the rationale for targeting HNHC ARFA is because of their disproportionate contribution to the overall alcohol burden on the NHS. No previous studies have evaluated the clinical and cost-effectiveness of AOT for HNHC ARFA: this RCT targeting ARFA across five South London NHS Trusts is the first to do so.

The inclusion criteria changed during recruitment to also include patients with alcohol related frequent emergency department attendances. In practice, this resulted in an increase in recruitment across the participating NHS trusts. Assessments completed by the AOT clinical team during the first 6 months of recruitment revealed that some participants had few inpatient hospital admissions in a year, but frequently attended an emergency department for alcohol related reasons, often choosing to leave before discharge. A high number of emergency department attendances with no resulting inpatient hospital admission incur costs of similar proportions to an inpatient hospital admission which are of importance to the economic analysis undertaken in the trial. A full amendment was approved to recruit from this patient population.

As far as we are aware, this is the first randomised controlled trial to evaluate AOT approaches for high cost high need alcohol related frequent attenders. The main strength of the study is that participants are randomized to receive the intervention or care as usual (control). By randomly allocating ARFA to control or intervention groups the impact of confounders (such as age, gender, ethnicity, levels of engagement with other services) as a source of bias are equally distributed between the intervention and control groups, and therefore minimised. The blinding of the researchers to treatment allocations reduces reporting bias. The economic analysis is carried out to include criminal justice sector resources which is recognised as an appropriate extension for drug and alcohol treatment evaluations.

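### The models for ED attendance and admissions are stated to adjust for SADQ, site, age and gender but not for prior service use, on which patients are selected and which is known before randomisation

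*Protocol article*

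**What the plan says.** All places are in the protocol article.

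- **Eligibility.** Criterion iii under Inclusion criteria has four limbs joined by OR. One is that the patient "has had two or more admissions in any of the participating NHS trusts for at least one wholly attributable alcohol diagnoses within a 1 year" span. One is that the patient "has had at least ten presentations to an emergency department in any of the participating NHS trusts within a 1 year period". One is four ED presentations within a month. The last combines both kinds of contact: the patient "has been admitted at least once for a wholly attributable alcohol diagnosis and had at least four presentations to an emergency department" within a year.
- **Amendment.** ED attenders were added while recruitment was under way: "The inclusion criteria changed during recruitment to also include patients with alcohol related frequent emergency department attendances" (Protocol amendments). As the reason, the Discussion reports that "some participants had few inpatient hospital admissions in a year, but frequently attended an emergency department for alcohol related reasons".
- **Outcomes.** The abstract lists ED attendance and number and length of admissions among the secondary outcomes. Less unplanned care is one of four secondary hypotheses.
- **Adjustment.** For the secondary models at 6 and 12 months, "these will be adjusted for covariates; SADQ, site, age and gender".
- **Stratification.** "Randomisation will be stratified by site and severity of alcohol dependence". Service use plays no part.
- **What is known before allocation.** Case finding uses the "number of admissions or emergency department attendances in the previous 12 months" (Identification and recruitment of potential participants). The AD-SUS interview at baseline covers the previous 6 months (Economic evaluation).

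**The concern.** The trial selects patients on the quantities that it later analyses as service-use outcomes, and the amendment widened the spread of those quantities. A patient can enter with two admissions and no required ED presentation. Another can enter with ten ED presentations and no required admission. Past ED and admission counts are therefore likely to predict later ones, and the Discussion itself describes differing patterns of use. None of SADQ, site, age and gender is a measure of past service use.

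A prognostic covariate left out of the model sends its variation into the residual. The confidence intervals for ED attendance and admissions are then wider than they need to be, in a trial that expects 128 patients at follow-up. The information that would narrow them is already collected.

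**Working it through.** The plan states no power, rate or variance for ED attendance or admissions, so there is no figure of its own to reproduce on this point. From the plan I take only the 64 patients per arm expected at follow-up (Sample size and power). The percentage changes in variance from the formula below do not depend on that number. All rates, shares and dispersions are assumptions.

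**1. Formula for counts.** Let a share q of patients enter by ED presentations only, with mean m1, and the rest have mean m2. Counts are negative binomial with dispersion k, and m = q·m1 + (1−q)·m2.
- Without route, variance per patient of the log mean: U = [q(m1 + k·m1²) + (1−q)(m2 + k·m2²) + q(1−q)(m1−m2)²] / m².
- With route: A = 1 / [q/(1/m1 + k) + (1−q)/(1/m2 + k)].
- SE of the log rate ratio = √(2 × variance / 64).

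**2. Routes about threefold apart** (m1 = 5, m2 = 1.5, q = 0.5, k = 1).
- m = 3.25. U = (16.875 + 3.0625)/10.5625 = 1.888, so SE = 0.243.
- A = 1/[(0.8333 + 0.6)/2] = 1.395, so SE = 0.209.
- Variance falls by 1 − 1.395/1.888 = 26%.

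**3. Routes 1.5-fold apart** (m1 = 3, m2 = 2, q = 0.5, k = 1).
- m = 2.5. U = (9 + 0.25)/6.25 = 1.480, so SE = 0.215.
- A = 1/[(0.75 + 0.6667)/2] = 1.412, so SE = 0.210.
- Variance falls by 4.6%. Over q = 0.1-0.5 and k = 0.5-2 the fall is 2-5%. At means of 4 and 3 it is 1-3%.

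**4. Wider grid.** With m1 = 4-6, m2 = 1.5-2, q = 0.3-0.5 and k = 0.5-2 the formula gives 11-42%. Every point on that grid has routes at least twofold apart, so it shows the favourable end.

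**5. Check against fitted models.** The formula is optimistic. In 300 simulated trials of 128 patients, fitted negative binomial models for the case in step 2 gave a variance lower by 20% (spread of estimates) or 17% (model SEs). A separate simulation (lower-rate mean 4, dispersion 1, treatment rate ratio 0.7, q = 0.25 or 0.5) gave these ratios of SE with route to SE without:

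| Route rate ratio | SE ratio | Variance lower by |
|---|---|---|
| 1.5 | 0.990-0.994 | 1-2% |
| 2 | 0.963-0.970 | 6-7% |
| 3 | 0.913-0.916 | 16-17% |
| 4 | 0.872 | 24% |

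**6. A linear outcome, as a rough guide for length of stay.** If the routes differ by D within-route SDs, the variance explained is R² = q(1−q)D²/(1 + q(1−q)D²). For q = 0.10-0.50 and D = 0.25-1.0, R² runs from 0.6% to 20%, so the SE is 0.3% to 11% smaller.

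**7. The baseline count instead of route.** With an assumed correlation r of 0.3-0.6 between baseline and follow-up use, the variance falls by r², that is 9-36%, and the SE by 5-20%.

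**The case against.** The strongest reply is that the covariate list is open. The Statistical analysis section promises suitable modelling and says that the plan will be refined and agreed with the Trial Steering Committee. The abstract says that outcomes will be compared with control for baseline measures specified in advance, and it lists prior service use among the baseline assessments. An added covariate in a secondary model is ordinary content for a later analysis plan. This much stands: the omission is not an error of validity and is easily mended. But the abstract names no covariate. The one place that names them for the clinical secondary models gives four, and service use is not among them. Permission to refine the list does not put it there.

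The second reply is that route is a poor label. This stands. The limbs overlap, one requires both an admission and four ED presentations, and patients who enter by admissions have no ceiling on ED use. A reader might infer two groups cleanly separated by design; criterion iii does not support that. Route is a coarse proxy for the counts, so the counts should come first.

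The third reply is that the size is unproven. This also stands. A reader might infer from the upper end of the grid that the loss is large, but no route mix or rate is given, and at a 1.5-fold difference the gain is close to nothing.

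Three further inferences go too far. The comparison is not biased, since allocation is random. A chance imbalance in route between arms is not a separate defect, because the confidence interval already allows for it. And unplanned care is not ranked as the main secondary hypothesis; the protocol lists four without ranking them.

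**Conclusion.** The point holds as a matter of precision in the secondary service-use outcomes. The stated adjustment set omits prior ED and admission counts, which help to decide eligibility, are known before randomisation and very likely predict the outcomes. The primary outcome, percent days abstinent, is not touched, and the randomised comparison remains valid.

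The size is unknown. On assumed rates, route alone would lower the variance for ED attendance by about 2-5% at a 1.5-fold difference between routes and about 17-26% at roughly threefold. The lower figure of the second range comes from fitted models and the upper from the formula. For number and length of admissions no rates or variances are given; the linear range is only a guide to length of stay. The baseline count probably recovers more than route, if its correlation with follow-up use is moderate. The case for the change rests on its very low cost rather than on a demonstrated large gain.

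**What to change.** In the models for ED attendance and for number and length of admissions, add the baseline value of the matching outcome to SADQ, site, age and gender: prior ED attendances for the ED model, prior admissions or days in hospital for the admission models. The source can be the 12-month records used in case finding or the baseline AD-SUS; name one in advance. Use the qualifying route under criterion iii (ED presentations only, or any limb with an admission) as an additional covariate, or as a fallback where the count is missing or unreliable.

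The Trial status section says that analysis is ongoing, so this should be written into the final analysis plan before unblinded results are seen. The cost is one or two degrees of freedom per model and no new data. An effect by route may be reported, but as exploratory only.
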